#### Exclusion criteria

2.8.2

Patients who meet any of the following conditions cannot participate in the trial:

1.Women who cannot undergo acupuncture treatment for 2 months2.Women who are taking or administer medicines and procedures related to pregnancy, such as hormones, herbal medicine, and moxibustion treatment3.Women whose menstrual cycle is irregular (<21 days, more than 40 days)4.Women whose partner is azoospermia5.Women diagnosed with ovulation disorders (polycystic ovary syndrome, thyroid disease, hyperprolactinemia, etc.)6.Women with physical or mental impairment who may be exposed to risk by participating in this clinical trial, who may cause confusion in results, or fail to comply with the requirements of the clinical trial7.Women who have a neurological or psychologically pathologic history or are currently suffering from a disease8.Women who cannot be treated with acupuncture due to skin diseases, such as ulcers or eczema9.Women who have participated in other clinical trials within the past 3 months10.Women who have a history of drug abuse and alcohol abuse within 5 years prior to clinical trial participation11.Women who have been diagnosed with infertility due to a deformity of the reproductive organs or leiomyoma12.Patients for whom the researcher considers that it would be difficult to perform the clinical trial

### Intervention

2.9

#### Arm 1: IVF-ET after acupuncture

2.9.1

The interventional protocol and the intensive choice of acupoints were based on the experiences of the KMD and from previous clinical studies (Table 1). See Fig. 1 for a flowchart of trial procedures. The acupoints of CV4 and CV3 will be applied on one side. The acupoints of EX-CA1, SP6, KI3, SP10, ST36, and LR3 will be applied on both sides. All acupoints will be limited to the locations defined by the WHO. During the treatment, participants will lie in the bed, and the KMD will use 75% alcohol pads to sterilize the skin around the acupoints. Subsequently, stainless steel sterilized needles (diameter 0.25 mm, length 3 cm, Dongbang Medical, Korea) will be inserted into the selected acupoints at depths of 0 to 20 mm for 30 minutes. During the acupuncture treatment period, the lower abdomen is irradiated with infrared rays. This group will undergo a total of 16 acupuncture treatments for approximately 8 weeks at 2-day intervals (+1 day) before inducing ovulation.

**Table 1 T1:**
[figure not shown]
Acupoints used in the acupuncture + in vitro fertilization and embryo transfer group.

#### Arm 2: IVF-ET

2.9.2

These participants will have no treatment for 2 months to compare with the Arm 1 group. The ovulation induction will then proceed according to the IVF-ET procedure.

### Outcome measurements

2.10

#### Primary outcome

2.10.1

The primary outcome will be measured based on the retrieval of mature oocytes at 10 weeks from baseline.

#### Secondary outcome

2.10.2

At 8 weeks from the baseline of the treatment period, patients will be assessed for AFC and AMH. The DASS-42 score will be measured at 4 and 8 weeks from baseline.

#### Other outcomes

2.10.3

At 10 weeks from baseline, the in vitro fertilization rate of retrieved oocytes will be assessed.

### Assessment analysis

2.11

#### Quality control and data monitoring

2.11.1

Independent of sponsors and competitive interests, CROcent will perform evaluation and monitoring to ensure the results and quality of the clinical trial. During the trial, CROcent will monitor regularly whether the study is proceeding in accordance with the protocol, through the use of all related master files such as documentation, case report forms, informed consent forms, and adverse event reports. When monitoring this trial, we will ensure that the clinical trial will be performed in accordance with the approved protocol and the GCP and related regulation, ensure that case report will be complete and clear, and check with the register.

#### Data collection, access, and management

2.11.2

The data of this trial will be managed according to the standard work instructions of Pusan University Hospital. Other contents not specified in the trial protocol shall follow the standards of the International Conference on Harmonization of Technical Requirements for Registration of Pharmaceuticals for Human Use (ICH)-Guideline for GCP and the Korean Good Clinical Practice guidelines.

The source document is recorded immediately when the case data are collected. After the source document input is completed, it will be recorded in the case record form. All the documents will be kept safe, so that it can be verified by the relevant government agencies and institutional review board (IRB). Only research colleagues and others who have the approval of the principal investigator have access to all data obtained from this trial.

#### General analysis

2.11.3

The statistical analysis will be conducted by blinded professional statisticians. Unless otherwise specified, all data will be based on a 2-sided test at a significance level of 5%. The continuous variable gives the number of observation, the mean ± stdev and the median (minimum values, maximum values), while the categorical variable gives the frequency and percentage. If missing values are found in continuous validation variables, they will be analyzed using the last observation carried forward method. At this time, the results before applying the clinical trial device (control randomized) will not be replaced by the results after applying the clinical trial device. If a categorical validation variable has a missing value, it will be considered a failure and included in the analysis. Safety assessment variables will not replace missing values.

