#### Baseline

2.7.2

(1)The baseline is the second day of menstruation. On the second day, information will be collected by performing history confirmation, previous drugs, vital signs, anti-Müllerian hormone (AMH) test, antral follicle count (AFC) using ovarian ultrasound, random assignment, and evaluation with the depression anxiety stress scales (DASS) 42.(2)One-time after-screening randomization is performed at a ratio of 1:1 eligible subjects on the second day of menstruation.Arm 1: IVF-ET after acupuncture.Arm 2: IVF-ET.

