#### Primary assessment

2.12.1

The primary endpoint will be the number of mature oocytes harvested at 10 weeks from baseline. The descriptive for each applied group will be presented and analyzed with the 2-sample *t* test or Wilcoxon rank-sum test depending on the satisfaction of normality.

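### Last observation carried forward cannot operate on the primary endpoint, a mature oocyte count taken once, so the plan has no working rule for women who never reach retrieval

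*Protocol article*

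**What the plan says.** Section 2.11.3 (General analysis) gives one rule for missing continuous efficacy variables: "If missing values are found in continuous validation variables, they will be analyzed using the last observation carried forward method". A limiting sentence follows: "the results before applying the clinical trial device (control randomized) will not be replaced by the results after applying the clinical trial device". Categorical variables have a different rule: "If a categorical validation variable has a missing value, it will be considered a failure and included in the analysis".

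Section 2.10.1 defines the primary outcome: "The primary outcome will be measured based on the retrieval of mature oocytes at 10 weeks from baseline". Section 2.12.1 repeats it as a count, "The primary endpoint will be the number of mature oocytes harvested at 10 weeks from baseline", to be "analyzed with the 2-sample *t* test or Wilcoxon rank-sum test depending on the satisfaction of normality".

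The baseline visit (2.7.2) collects "anti-Müllerian hormone (AMH) test, antral follicle count (AFC) using ovarian ultrasound, random assignment, and evaluation with the depression anxiety stress scales (DASS) 42", with no oocyte count. Section 2.10.2 places AFC and AMH at week 8 and adds: "The DASS-42 score will be measured at 4 and 8 weeks from baseline".

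Section 2.6 lists the reasons for early termination or dropout. They include withdrawal of consent, adverse events, need for interfering drugs, loss to follow-up and natural pregnancy. Section 2.4 allows for 10% dropout by recruiting 35 per arm for 31 needed.

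**The concern.** Carrying a value forward needs an earlier value of the same variable. The endpoint that decides this trial has none, so the only stated rule for a missing count returns nothing. The rule for categorical variables does not reach a count. A test that needs one number per woman then runs, by default, on the women who have one.

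That subset is formed after randomisation. In women selected for a poor ovarian response, failing to reach retrieval is plausibly related to the outcome itself. The trial is open and the arms are handled differently: Arm 1 has 16 treatment visits, while section 2.7.3 schedules no separate visit for Arm 2 for about 8 weeks. The Discussion also asks Arm 2 women to avoid alternative treatments and, in unclear wording, seems to link failure to do so with leaving the study. The chance of reaching retrieval could therefore differ by arm, and a comparison limited to women with a count would no longer compare the groups as randomised.

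**Working it through.** **Step 1. What could be carried forward?** Times are from sections 2.7.2, 2.10.1, 2.10.2 and 2.12.

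| Variable | Earlier in-trial values | Assessed at | Effect of carrying forward |
|---|---|---|---|
| Mature oocytes (primary) | none | week 10 | impossible |
| AFC, AMH | baseline | week 8 | assumes no change from baseline |
| DASS-42 | baseline; week 4 for the week-8 score | weeks 4 and 8 | possible |

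The only other oocyte count mentioned is a past poor response in inclusion criterion 5b. It is one of three items of which two are required, so not every woman has one, and it predates the trial.

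For AFC and AMH, the limiting sentence in 2.11.3 concerns substitution between results before and after the intervention. Its wording does not settle whether a baseline value may stand in for a missing week-8 value.

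**Step 2. Reproduce the plan's own figure.** Inputs from section 2.4: means 4.87 and 2.38, SD 3.47, two-sided 5%, 80% power, 1:1.

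- Difference: 4.87 − 2.38 = 2.49.
- n per arm = 2 × (1.960 + 0.842)² × 3.47² / 2.49² = 30.5, rounded up to 31.
- With 10% dropout: 31 / 0.90 = 34.4, rounded up to 35.

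The stated 31 and 35 reproduce. Power at 31 per arm is 80.7% by the normal approximation and 79.4% by the noncentral t. The sample size treats the other 4 per arm as contributing no count, which fits the inference that they leave the analysis. The size allows for this loss; the issue is bias.

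**Step 3. How far could the answer move?** These are illustrations. Assumptions: women with a count have means 4.87 and 2.38 and SD 3.47 in both arms; f₁ (acupuncture) and f₂ (control) are the shares without a count; every such woman is scored 0. The shares are assumed. Scoring all of them 0 is harsher than the rule proposed below.

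Difference over all randomised women = 4.87(1 − f₁) − 2.38(1 − f₂). Variance per arm = (1 − f) × 3.47² + f(1 − f) × mean². Power is by noncentral t with 35 randomised per arm.

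| f₁ / f₂ | Women with a count only: difference (power) | Missing scored 0: difference (power) |
|---|---|---|
| 10% / 10% | 2.49 (80.0%) | 2.24 (75.5%) |
| 20% / 20% | 2.49 (75.1%) | 1.99 (66.0%) |
| 20% / 0% | 2.49 (79.5%) | 1.52 (41.8%) |
| 0% / 20% | 2.49 (79.5%) | 2.97 (95.4%) |
| 10% / 20% | 2.49 (77.5%) | 2.48 (84.7%) |

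With exactly 4 of 35 lost in each arm: 4.87 × 31/35 = 4.31; 2.38 × 31/35 = 2.11; difference 2.21 after rounding (2.49 × 31/35). The analysis of women with a count would then overstate the difference by 0.28.

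**Step 4. No difference among women with a count.** With a common mean of 2.38 (assumption), 20% / 10% gives 2.38 × (0.80 − 0.90) = −0.24, and 20% / 0% gives 2.38 × (0.80 − 1.00) = −0.48. The analysis restricted to women with a count shows 0 in both cases.

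**The case against.** The strongest reply is that the article condenses a fuller protocol (Version 2.0 is cited in 2.2), and that analysis sets and the counting of cancelled cycles are commonly left to that document or the analysis plan. That stands as far as omissions go: the article nowhere says that women without retrieval are excluded, and the restriction to women with a count is an inference. It does not rescue the rule that is stated. Last observation carried forward is fixed for all continuous efficacy variables, and it cannot do its work on the most important one.

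Several stronger readings are tempting and are not supported:

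- A reader might infer that a woman whose retrieval yields no mature oocyte is treated as missing. Nothing says so. Her count is an observed 0 and enters the test.
- A reader might infer from the absence of a separate Arm 2 visit before about 8 weeks (2.7.3) that carrying DASS-42 forward would work only in Arm 1. Section 2.10.2 gives the week-4 measurement without limiting it to one arm, both arms have a baseline score, and the document does not say that the questionnaire needs a visit. Sections 2.7.3 and 2.10.2 should be reconciled, but the asymmetry is not established.
- A reader might set the lost control women alone to 0 and conclude that the effect is understated. Equal loss in both arms points the other way. The 10% in section 2.4 is also general dropout, with causes such as withdrawn consent and natural pregnancy that are not true zeros.

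The trial is labelled exploratory. That lowers the stakes of one result but does not make an inoperable rule for its primary endpoint acceptable.

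**Conclusion.** The point holds in this form: the stated missing-data rule cannot operate on the primary endpoint, no other stated rule covers a missing count, and following the text as written leaves, by inference, only women who reach retrieval. The mismatch is certain from the document. The bias is conditional: under the Step 3 assumptions it ranges from an overstatement of 0.97 oocytes (2.49 − 1.52) to an understatement of 0.48 (2.97 − 2.49), and can be close to nil (10% / 20%). Whether the reference study's means already include zeros cannot be seen. Neither direction nor size can be determined here, which is why the rule should be settled before outcome data are seen.

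For AFC and AMH the defect is smaller: carrying forward could only assume no change from baseline, and whether that is permitted is unclear.

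**What to change.** Replace last observation carried forward for the primary endpoint with a rule along these lines:

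1. Analyse all randomised women in the arm to which they were allocated.
2. Count a cycle that was started and then cancelled before retrieval as 0 mature oocytes. State that a retrieval yielding none is an observed 0.
3. For women who stop study procedures, use the retrieval result from clinic records where consent allows.
4. Handle other missing counts by multiple imputation using arm, age, baseline AFC and baseline AMH.
5. State separately how natural pregnancy before stimulation enters the analysis; it should not be a routine zero.
6. Add a sensitivity analysis that varies the assumption about missing counts by arm.

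For AFC, AMH and DASS-42, use models adjusted for the baseline values already collected instead of carrying values forward. Clarify or delete the limiting sentence in 2.11.3.

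The cost is revised wording, somewhat more analysis work and some effort to obtain clinic records. No extra patients or visits are needed. The estimated difference may come out smaller.

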#### Treatment period

2.7.3

(1)Arm 1: IVF-ET after acupunctureThe KMD begins acupuncture treatment from the random allocation date of the subjects. The subject will be administered acupuncture treatment at 2-day (+1 day) intervals until the beginning of the third menstrual period (approximately 8 weeks) for a total of 16 acupuncture visits.(2)Arm 2: IVF-ETThe subjects are not scheduled to visit a separate clinical trial until approximately 8 weeks (28 day ± 1) from the date of randomization, when they present for oocyte collection.

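### The limit on carry-forward in section 2.11.3 is worded in reverse, so a baseline AFC, AMH or DASS-42 value may fill a missing follow-up value

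*Protocol article*

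**What the plan says.** Section 2.11.3 (General analysis) gives one rule for missing continuous outcomes: "If missing values are found in continuous validation variables, they will be analyzed using the last observation carried forward method". The next sentence limits it: "the results before applying the clinical trial device (control randomized) will not be replaced by the results after applying the clinical trial device". No other section restricts which values may be carried.

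The measurement schedule decides what there is to carry:

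- **Baseline (2.7.2).** The visit on the second day of menstruation includes "anti-Müllerian hormone (AMH) test, antral follicle count (AFC) using ovarian ultrasound, random assignment, and evaluation with the depression anxiety stress scales (DASS) 42".
- **AFC and AMH (2.10.2).** There is one follow-up: "At 8 weeks from the baseline of the treatment period, patients will be assessed for AFC and AMH".
- **DASS-42 (2.10.2).** There are two follow-ups: "The DASS-42 score will be measured at 4 and 8 weeks from baseline". No restriction by arm is stated.
- **Visits (2.7.3).** Arm 1 is treated "until the beginning of the third menstrual period (approximately 8 weeks) for a total of 16 acupuncture visits". Arm 2 has no separate trial visit scheduled until about 8 weeks after randomisation, but the bracket beside that figure gives 28 days plus or minus 1, which is 4 weeks.
- **Primary endpoint (2.12.1).** "The primary endpoint will be the number of mature oocytes harvested at 10 weeks from baseline". No baseline oocyte count is listed.

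Section 2.12.2 compares the arms on the secondary outcomes with a two-sample t test, or for DASS-42 a Wilcoxon test if normality fails.

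**The concern.** A limit on carry-forward normally says that a pre-treatment value must not stand in for a post-treatment value. Here the roles are swapped: the pre-treatment result is protected from being overwritten by a later one. Carry-forward only moves values forward in time, so the limit restricts nothing.

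A programmer who follows the text would give a woman with no week-8 AFC or AMH her own baseline value, a change of exactly zero. A missing week-4 DASS-42 would be handled in the same way. Three secondary outcomes are at stake. A real effect would be diluted by the share of women filled in, and filled-in values would enter the test as if observed. If the share filled differed between arms while values drifted in both, part of the drift would appear as an arm difference.

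**Working it through.** **1. The plan's own figures.** Section 2.4 gives means of 2.38 and 4.87 (difference 2.49), SD 3.47, two-sided 5%, 80% power and 1:1 allocation. n per arm = 2 × (1.960 + 0.842)² × 3.47² / 2.49² = 30.5, so 31. With 10% dropout, 31 / 0.90 = 34.4, so 35. Both figures reproduce and neither is in dispute. The 10% is the only missing-data figure in the article.

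**2. What can be carried into each slot.**

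| Missing value | Earlier values | Sentence as written | Sentence reversed (baseline never carried) |
|---|---|---|---|
| Week-8 AFC, AMH | baseline only | baseline | stays missing |
| Week-4 DASS-42 | baseline only | baseline | stays missing |
| Week-8 DASS-42 | baseline, week 4 | week 4, or baseline if week 4 is also missing | week 4 if observed |
| Week-10 mature oocytes | none listed | nothing to carry | nothing to carry |

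**3. Dilution of a true effect.** Let a and c be the true mean changes in Arms 1 and 2, and m1 and m2 the shares filled with baseline. The apparent difference is (1 − m1)·a − (1 − m2)·c. The effect sizes below are illustrative; the article gives none for AFC or AMH.

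- a = 0.70 SD, c = 0, 10% filled in each arm: 0.90 × 0.70 = 0.63 SD (simulated 0.634).
- The same with 20% filled: 0.80 × 0.70 = 0.56 SD (simulated 0.560).
- a = 0.50 SD, c = 0, 20% filled in Arm 1 and 10% in Arm 2: 0.80 × 0.50 = 0.40 SD.

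Power is hardly the issue. With a standardised effect of 2.49 / 3.47 = 0.718, borrowed from the oocyte assumption, and 4 of 35 women per arm filled with zero change, simulated power is 79.2%. Analysing only the 31 observed per arm gives 79.4%. The damage is to the size of the estimate.

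**4. False-positive rate for week-8 AFC or AMH.** No true arm difference, the same change in both arms, 35 per arm, correlation 0.6 between baseline and week 8. Loss, drift and correlation are assumptions.

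| Loss, one arm / other arm | Common change | Rejection at 5% |
|---|---|---|
| 10% / 10% | 0.5 SD | 5.0% |
| 5% / 15% | 0.2 to 0.5 SD | 5.0 to 5.8% |
| 5% / 20% | 0.5 SD; 1 SD | 6.1%; 9.2% |
| 5% / 30% | 0.5 SD; 1 SD | 7.3%; 16.8% |

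Observed values with baseline as covariate rejected in 4.4 to 5.7% of runs in the 5% / 20% and 5% / 30% settings. With no change over time in either arm, the formula in step 3 gives no bias at all.

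**The case against.** **It is a translation slip.** Very likely. Placed straight after the carry-forward rule, the sentence makes sense only if it was meant to keep baseline out of follow-up. On that meaning, AFC, AMH and week-4 DASS-42 simply stay missing, and the dilution in step 3 does not arise. This bears on how serious the point is. It does not make the text right: the printed rule permits what it was presumably meant to forbid.

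**The analysis plan may handle it.** This is not a complaint that something is left out. The article states a rule and states it wrongly.

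**A stronger reading that does not hold.** A reader might infer that week-4 DASS-42 is missing for all of Arm 2, so that the whole arm is filled with baseline and Arm 1 is tested against a change fixed at zero. If that happened, with 35 per arm, no true effect and correlation 0.5 to 0.7, a change-score t test would reject in 22 to 33% of trials for a common drift of 0.2 SD, 42 to 62% for 0.3 SD and 83 to 96% for 0.5 SD. The article does not establish this. Section 2.10.2 schedules DASS-42 at week 4 without restriction by arm. Section 2.7.3 describes visits and does not exclude remote completion. Its bracket of 28 days leaves open whether a contact near week 4 exists. What stands is a discrepancy between the two sections, with a conditional risk that Arm 2 loses more week-4 scores than Arm 1.

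**Unequal loss of AFC and AMH.** The article gives no loss by arm for these outcomes, only 10% overall. The larger rates in step 4 are therefore not predictions.

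**The fix is larger than the defect.** Partly fair. Reversing the sentence would alone keep baseline values out of follow-up. It would still let week-4 DASS-42 scores fill week 8. The fuller change uses baseline values already collected, but it must also reach section 2.12.2 or the protocol will contradict itself.

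**Conclusion.** Wrong as written. The limit in section 2.11.3 is reversed, and nothing else in the article stops a baseline value from filling a missing follow-up value.

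Followed literally, the rule dilutes a true AFC or AMH effect by the share of women missing, about one tenth at the planned dropout if that share applies to week 8. The false-positive rate stays near its nominal level unless loss differs by arm and values drift over time. Both would have to be assumed. A heavier effect on Arm 2 for week-4 DASS-42 is possible but depends on how that score is collected, which the article leaves unclear.

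The primary oocyte count is untouched, and the trial calls itself exploratory. This is a worthwhile correction to secondary analyses and does not threaten the main result.

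**What to change.** 1. In 2.11.3, replace the carry-forward rule and its limit, for AFC, AMH and DASS-42, with wording such as: *No pre-randomisation value is used as a follow-up value. Missing AFC, AMH and DASS-42 values are not carried forward. Observed follow-up values are analysed with the baseline value as covariate; for DASS-42, in a repeated-measures model over weeks 4 and 8.*
2. Amend 2.12.2 so that the tests named there match.
3. Reconcile 2.7.3 with 2.10.2: state how week-4 DASS-42 is obtained in Arm 2, and resolve 8 weeks against 28 days. If no week-4 score is obtained in Arm 2, make no between-arm test at week 4.

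The cost is a change of wording, a little more programming, and slightly wider intervals where values are missing. The 31 and 35 per arm are unaffected, and the analysis change needs no extra patients or visits.
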